## Abstract

**Introduction:**

Routine histopathological examination following appendicectomy and cholecystectomy has significant financial implications and comprises a substantial portion of the pathologists’ workload, while the incidence of unexpected pathology is low. The aim of the selective histopathological examination Following AppeNdicectomy and CholecystectomY (FANCY) study is to investigate the oncological safety and potential cost savings of selective histopathological examination based on macroscopic assessment performed by the surgeon.

**Methods and analysis:**

This is a Dutch multicentre prospective observational study, in which removed appendices and gallbladders will be systematically assessed by the operating surgeon for macroscopic abnormalities suspicious for malignant neoplasms. After visual inspection and digital palpation of the removed specimen, the operating surgeon will report whether macroscopic abnormalities suspicious for a malignant neoplasm are present, and if he or she believes additional microscopic examination by the pathologist is indicated. Regardless of the surgeon’s assessment, all specimens will be sent for histopathological examination. In this way, routine histopathological examination can be compared with a hypothetical situation in which specimens are routinely examined by surgeons and only sent to the pathologist on indication. The two main outcomes are oncological safety and potential cost savings of a selective policy. Oncological safety of selective histopathological examination will be assessed by calculating the number of patients in whom a histopathological diagnosis of an appendiceal neoplasm or gallbladder cancer with clinical consequences benefitting the patient would have been missed. A cost analysis will be performed to quantify the potential cost savings.

**Ethics and dissemination:**

The study protocol was reviewed by the Institutional Review Board of the Amsterdam UMC, location AMC, which decided that the Dutch Medical Research Involving Human Subjects Act is not applicable. In all participating centres, approval for execution of the FANCY study has been obtained from the local Institutional Review Board before the start of inclusion of patients. The study results will be disseminated through peer-reviewed publications and conference presentations. Guidelines will be revised according to the findings of the study.

**Trial registration number:**

NCT03510923.

Strengths and limitations of this studyThis will be the first multicentre study that prospectively investigates both the oncological safety and potential cost savings of selective histopathological examination following appendicectomy and cholecystectomy in a large cohort of patients.The robust and transparent instruction on how to perform a proper macroscopic assessment of the removed specimens results in a uniform performed examination.As a result of the high participation rate of Dutch hospitals, a large number of surgeons and residents will become experienced in performing macroscopic examination of appendices and gallbladders, which will ease successful implementation of a selective policy, if oncological safety is proven.Patients’ safety will not be compromised, since all specimens will be routinely sent for additional microscopic examination by the pathologist, regardless of the surgeon’s assessment.Due to limited and inconclusive evidence on the prognostic impact of revisional surgery in patients with gallbladder cancer, all additional diagnostic or therapeutic procedures that performed ≥T1 b gallbladder were considered beneficial.

## Introduction

In the Netherlands, approximately 16 000 appendicectomies and 22 500 cholecystectomies are performed annually. Traditionally, all removed appendices and gallbladders are microscopically examined by a pathologist to exclude the presence of a malignancy. However, most specimens show typical histopathological findings and unexpected neoplasms are only diagnosed in less than 1%.^1 2^ At the same time, histopathological examination (HPE) of the appendix and gallbladder constitutes a significant financial burden on healthcare, and comprises a considerable portion of the pathologists’ workload. Consequently, it is debatable whether routine HPE following appendicectomy and cholecystectomy is necessary.

In the past decade, several studies suggested that a selective HPE policy might be justified.^3–8^ Selective HPE entails that surgeons perform a macroscopic assessment of the removed specimen, and select specimens that require additional microscopic examination by the pathologist. Opponents fear that surgeons might not recognise neoplasms, resulting in missed diagnoses with potential disadvantageous consequences for the patient. However, it is hypothesised that tumours not detected during visual inspection or palpation are of early stage. These missed tumours are likely to be clinically inconsequential after the appendix or gallbladder have been completely resected. Most appendiceal neoplasms are neuro-endocrine tumours, which only require additional treatment if the diameter exceeds 2 cm or if the tumour exhibits unfavourable histopathological characteristics.^9^ In case of gallbladder cancer (GBC), an extended cholecystectomy is only indicated for stage T1b and above.^10^ Unfortunately, prospective studies regarding macroscopic assessment of appendiceal specimens by the surgeon are lacking, and the few prospective studies investigating the ability of surgeons to identify macroscopic abnormalities in gallbladder specimens are limited by the small numbers of patients.^11–13^

Currently, it is still standard practice in the Netherlands to send all appendices for HPE.^14^ The Dutch guideline for gallstone disease states that macroscopic normal appearing gallbladders can be refrained from HPE.^15^ However, implementation of this recommendation appeared to be suboptimal, and the need for more evidence was expressed.^16^ In order to draw definitive conclusions regarding safety and potential cost savings of a selective policy, a large prospective cohort of patients is required. The FANCY study will prospectively investigate the ability of surgeons to macroscopically recognise neoplasms with clinical consequences in a multicentre setting, resulting in definitive recommendations regarding the appropriate HPE policy of appendices and gallbladders.

## Methods and analysis

### Objectives

The primary aim of this study is to determine whether a selective HPE policy following appendicectomy and cholecystectomy for presumed benign diseases is oncologically safe. In addition, we will quantify the potential cost savings of selective HPE.

### Study design

This is a Dutch multicentre prospective observational study, registered with ClinicalTrials.gov on 27 April 2018. The study was designed in accordance with the principles of collaborative resident-led snapshot research. This type of research is primarily led and conducted by surgical residents, supervised by consultants. Snapshot research is particularly suited to investigate a common condition or treatment. By generating a population-based overview, this design rapidly provides insight in current clinical practice. Previous snapshot studies performed by the Dutch Snapshot Research Group on appendicitis, rectal cancer, and acute left-sided obstructive colon cancer demonstrated that many data can be collected in a short period of time.^17–19^

In the FANCY study, appendices and gallbladders will be systematically assessed by the operating surgeon (or surgical resident) for macroscopic abnormalities suspicious for malignant neoplasms. After visual inspection and digital palpation of the removed specimen, the operating surgeon will report on a predefined scoring form whether macroscopic abnormalities suspicious for a malignant neoplasm are present, and if he or she believes additional microscopic examination by the pathologist is indicated (online supplementary material 1). In case of suspicious macroscopic abnormalities, the surgeon is asked to describe these on the same form. Similarly, the surgeon is requested to specify the indication for HPE, if present. Regardless of the surgeon’s assessment, all specimens will be sent for HPE. In this way, routine HPE can be compared with a hypothetical situation of selective HPE.

10.1136/bmjopen-2019-035912.supp1Supplementary data

The FANCY study will be performed in 60 out of 74 Dutch hospitals, including academic (n=6), teaching (n=37) and non-teaching hospitals (n=17). Centres that have already implemented a selective HPE policy for gallbladder specimens may choose to either only participate in the appendix part of the FANCY study or to return to the routine policy for the duration of the study period. Hospitals will be allowed to start patient accrual after local approval has been obtained, and a site initiation visit has taken place, including a presentation of the study protocol and instructions for the macroscopic assessment of the specimens. Due to variation in completion of hospitals’ local approval procedures, it was decided to open study sites in phases. Every first day of a new month, a group of hospitals will start patient accrual. To avoid bias, all hospitals will include patients for a duration of 9 months, even if this means that the required sample size is exceeded.

### Study population

Patients of all ages scheduled to undergo appendicectomy for appendicitis or cholecystectomy for cholecystitis or gallstone disease in the elective or non-elective setting will be included.

A potential subject who meets any of the following criteria will be excluded:

#### Appendix

Primary indication for surgery: strong clinical/radiological suspicion or histopathological proof of an appendiceal neoplasm.Appendix removed as part of more extensive surgery, so-called incidental appendicectomies (eg, right colectomy).Patients included in the The effect of Appendectomy on the Clinical Course of UlceRatiVe colitis (ACCURE) trial.^20^

#### Gallbladder

Primary indication for surgery: strong clinical/radiological suspicion or histopathological proof of GBC.Gallbladder removed as part of more extensive surgery, so-called incidental cholecystectomies (eg, Whipple procedure).The presence of a polyp of >10 mm on preoperative imaging.

### Study observations

#### Macroscopic assessment

During the site initiation visits, all steps of a systematically performed macroscopic assessment will be discussed. Instruction videos showing how to perform the macroscopic assessment will be available on the study website during the entire study period.

#### Surgeon’s macroscopic assessment of the appendix

The examination starts with inspection of the appendix and mesoappendix, followed by digital palpation. In consultation with the pathologist, it was decided that opening the appendix is prohibited, since this might impede proper HPE.

#### Surgeon’s macroscopic assessment of the gallbladder

First, the outer surface of the gallbladder is inspected. Then, the gallbladder is incised along its longitudinal axis on the peritoneal side, leaving the cystic duct intact. After removal of stones and bile, the gallbladder mucosa is inspected and palpated. Examples of macroscopic abnormalities are masses, polyps, ulcers, cysts, hardening, irregularity and wall thickening.

#### Histopathological examination

All specimens will be sent to the department of pathology for macro/microscopic assessment. HPE will be conducted according to the local protocol of the pathology department where the specimen is assessed. In general, this includes macroscopic assessment of the complete specimen, followed by microscopic assessment of samples taken from macroscopic abnormalities and the top (in case of appendices) or cystic duct margin (in case of gallbladders). If no macroscopic abnormalities are present, random samples are taken for microscopic assessment. The latest histological tumour–node–metastasis (TNM) classification of the American Joint Committee on Cancer applicable at the time HPE was performed was used for staging malignancies.^21^

#### Additional treatment

In case of a histopathologically proven appendiceal neoplasm or GBC, the postoperative management will be discussed in a local multidisciplinary team meeting. If it is decided that an additional resection is required, the specimens of the re-resection will be evaluated for the presence of residual tumour and positive lymph nodes, according to the local protocol.

### Outcomes

All outcomes will be analysed separately for appendiceal and gallbladder specimens.

#### Primary outcomes

##### Oncological safety

Oncological safety of selective HPE will be assessed by calculating the number of patients per 1000 examined appendices or gallbladders with the histopathological diagnosis of an appendiceal neoplasm or GBC with clinical consequences benefitting the patient that would have been missed. In case of an appendiceal neoplasm, the following consequences will be considered beneficial: (1) HPE of the re-resection specimen shows residual tumour and/or positive lymph nodes, (2) treatment with (adjuvant) systemic or local chemotherapy, radiotherapy, immunotherapy or stem cell transplantation and (3) palliative treatment for metastases detected during staging procedures. If an additional resection is performed following the diagnosis of an appendiceal neoplasm, and no residual tumour and/or positive lymph nodes are found during HPE, this is considered harmful due to the potential risks of surgery the patient is exposed to. For GBC, evidence on the prognostic impact of revisional surgery and adjuvant therapies is limited and inconclusive.^22^ For pragmatic reasons, it was decided that all cases of GBC requiring additional diagnostic or therapeutic procedures (ie, ≥T1 b GBC) will be considered beneficial.

To determine the number of missed diagnoses, only the specimens that would not have been sent for HPE in case of a selective policy (ie, specimens without an indication for HPE according to the surgeon) will be analysed. In general, it is difficult to determine what incidence of missed neoplasms is acceptable to omit routine HPE. The cut-off value for safety of selective HPE was chosen based on data from the Dutch national screening programme for colorectal cancer (CRC). The incidence of CRC in asymptomatic patients is 0.8%, and the sensitivity of the immunochemical faecal occult blood test (iFOBT) ranges from 65%-80%, depending on the number of screenings.^23^ As a result, the diagnosis of CRC is missed in 1.6–2.8 per 1000 patients. Since selective HPE implies cost savings, a reduced workload for pathologists, and less risk of overtreatment, a higher incidence of missed diagnoses is acceptable. Therefore, it was decided that selective HPE of appendices and gallbladders will be considered oncologically safe if the number of patients with a neoplasm with clinical consequences benefitting the patient that would have been missed is below 3 per 1000 examined specimens (approximately twice the incidence of missed CRC in the screening programme).

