### Group size calculation

Group size calculation is based on the number of appendices and gallbladders with a tumour with clinical consequences benefitting the patient that would have been missed in case of a selective policy. According to systematic reviews, the incidences of appendiceal neoplasms and GBC are 7 per 1000 and 4 per 1000 patients, respectively.^1 2^ Data regarding the ability of surgeons to recognise these abnormalities and the consequences of these neoplasms are insufficient. It is however estimated that less than 1 out of 1000 examined specimens will contain an appendiceal neoplasm or GBC with clinical consequences benefitting the patient that is not recognised by the surgeon during the macroscopic assessment. Selective HPE will be considered safe if this number does not increase to 3 per 1000 patients. To demonstrate non-inferiority of selective compared with routine HPE, a sample size of 4462 per cohort achieves a 84% power to detect a difference of 0.002 using a one-sided binomial test at a target significance level of 0.025, assuming a baseline and actual proportion of 0.001, and a non-inferiority limit of 0.00299. The actual significance level achieved by the Fisher's exact test is 0.021. These two cohorts (one for appendices, one for gallbladders) only include the specimens that would not have been sent for HPE in case of a selective policy. If the rate of HPE can be reduced to 20%, 5578 patients per cohort (4462/0.8) should initially be included.

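### The appendix benefit list counts metastases found at staging only when treatment is palliative, so curative treatment by local means alone can escape the missed count

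*Protocol article*

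**What the plan says.** The Oncological safety section under Primary outcomes defines a missed appendix case as a neoplasm with at least one of three consequences:

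- The first item rests on the pathology of a further operation: "1) HPE of the re-resection specimen shows residual tumour and/or positive lymph nodes".
- The second item rests on the type of therapy given, whatever its intent: "2) treatment with (adjuvant) systemic or local chemotherapy, radiotherapy, immunotherapy or stem cell transplantation".
- The third item alone names a staging finding: "3) palliative treatment for metastases detected during staging procedures".

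The next sentence deals with an additional resection after which "no residual tumour and/or positive lymph nodes are found during HPE, this is considered harmful". For gallbladder cancer the rule is broader: it counts "all cases of GBC requiring additional diagnostic or therapeutic procedures", that is, stage T1b and above.

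The Additional treatment section says only that "the specimens of the re-resection will be evaluated for the presence of residual tumour and positive lymph nodes", following the local protocol. It does not say whether an excised metastasis is a re-resection specimen, or whether tumour in it is residual tumour.

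The safety rule, in the Oncological safety part of the predefined statistical analysis plan, requires the one-sided 97.5% exact upper limit of the missed proportion to lie below 3 per 1000 specimens that would not have been sent.

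**The concern.** Item (3) is the only item that names a finding at staging, and it is tied to palliative intent. Two patients with the same missed neoplasm and the same staging finding can therefore be scored differently. The one treated palliatively is a missed case. The one whose metastases were ablated, or excised without any item (2) therapy, may not be. If the second patient also had a bowel re-resection that showed no tumour, the harm sentence applies to that operation. The article gives no reason for scoring the two differently.

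The error has one direction. A case that is not scored can only lower the missed count and so favours a verdict of safe. The Dissemination section says that guidelines will be adjusted according to the results, so the rule should not lean that way even slightly.

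**Working it through.** **Step 1. Run possible courses through the list.** All rows are patients whose specimen the surgeon would not have sent and in whom staging found metastases.

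| Course after diagnosis | Item met | Counted as missed? |
|---|---|---|
| Palliative treatment of the metastases | (3) | Yes |
| Curative intent, including any drug, radiation or transplant therapy in item (2) | (2) | Yes |
| Curative intent, with a re-resection specimen showing residual tumour or positive nodes | (1) | Yes |
| Curative excision of metastases, no item (2) therapy, no other positive specimen | (1) only if the excised metastasis is read as residual tumour in a re-resection specimen | Not settled |
| Curative ablation, no specimen, no item (2) therapy | None | No |
| Curative ablation as in the row above, plus a negative bowel re-resection | None | No; the re-resection is scored as harm |

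The gap is the last two rows and, on the narrow reading, the fourth.

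**Step 2. Reproduce the plan's own figures.** Inputs from Group size calculation: "a sample size of 4462 per cohort achieves a 84% power to detect a difference of 0.002" and "using a one-sided binomial test at a target significance level of 0.025", a true proportion of 0.001 and a limit of 0.00299.

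- Critical value: the largest c with P(X ≤ c | n = 4462, p = 0.00299) ≤ 0.025 is c = 6.
- Attained level: P(X ≤ 6 | 4462, 0.00299) = 0.0210 (stated 0.021).
- Power: P(X ≤ 6 | 4462, 0.001) = 0.836 (stated 84%).
- Inflation: 4462/0.8 = 5577.5, rounded up to 5578 (stated 5578).

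All reproduce. The wording gap makes no stated figure wrong.

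**Step 3. What one unscored case can do.** The exact one-sided 97.5% upper limit for x events in n is the 0.975 quantile of Beta(x + 1, n − x).

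| x / n | Upper limit per 1000 | Verdict |
|---|---|---|
| 6 / 4462 | 2.92 | Safe |
| 7 / 4462 | 3.23 | Not safe |
| 8 / 5522 | 2.85 | Safe |
| 9 / 5522 | 3.09 | Not safe |

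Here 5522 = 0.8 × 6902, rounded up. It combines the appendix accrual reported in Current status of the study, which was not yet final, with the planning assumption that 80% would not be sent.

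At n = 4462, one omission reverses the verdict when there are exactly 7 true events and one of them falls in the gap. The probability of exactly 7 events is about 8% at a true rate of 1 per 1000, and about 15% at an assumed 1.5 per 1000. These are chances of standing at the boundary, not of a gap case occurring.

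**Step 4. Sensitivity to the share lost.** The documents give no figure for the share f of true events that falls in the gap, so f is assumed. The chance of declaring safety is P(X ≤ 6 | 4462, p(1 − f)).

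| Assumed f | True rate 1 per 1000 | True rate 3 per 1000 |
|---|---|---|
| 0 | 83.6% | 2.0% |
| 5% | 86.3% | 3.0% |
| 10% | 88.8% | 4.4% |
| 20% | 92.9% | 9.1% |

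In this calculation, the false-safe rate at the limit stays close to the nominal 2.5% only if f is small. At f = 5% it is already slightly above.

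**The case against.** The strongest reply is that the gap is very small and partly a matter of reading. Items (1) and (2) do not depend on intent; in item (2) the word adjuvant is in brackets. The Additional treatment section does not confine re-resection to the bowel, so an excised metastasis may fairly be read as residual tumour. On that reading only treatment that yields no specimen is left out. To fall there, a patient needs an unsent specimen, a neoplasm, metastases at staging, local curative treatment only and no item (2) therapy, when the plan expects fewer than 1 missed event of any kind per 1000 (about 4.5 in 4462). Table 7 also lists additional diagnostic and therapeutic procedures for each case, so an affected patient would be visible. All of this stands, and it sets the size of the point.

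It does not remove the point. Table 7 shows the case but the list scores it, and on the list as written an ablated metastasis does not count. Nor is this detail left to a fuller document: the article states the rule, and the rule carries the restriction.

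Three stronger readings are tempting and are not supported:

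- A reader might infer that the list leaves out curative treatment of metastases in general. Items (1) and (2) already count most of it.
- A reader might infer that the list leaves out the patients who gained most. The documents do not rank the benefit of curative against palliative treatment.
- A reader might want a second, unrelated tumour found at staging to count as well. The outcome concerns consequences of the appendiceal neoplasm, and adding such tumours would widen the endpoint rather than correct it.

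The contrast with the gallbladder rule shows only that the restriction is not built into the design. The article says that the broader gallbladder rule was chosen for pragmatic reasons.

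**Conclusion.** The point holds in a narrow form. Item (3) is tied to palliative intent, so a missed patient whose metastases were treated for cure by local means alone meets no item on the list. Ablation without item (2) therapy or a positive re-resection specimen is clearly outside it. Excision is outside only if the excised tissue is not read as residual tumour, which the article leaves open.

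The number of such patients is not given; none, one or two is an assumption. The sample size and power stand as computed. The verdict changes only if the count lies at the boundary and a gap case exists, and the change is then always from not safe to safe. It is a minor defect in the wording of the primary outcome, worth correcting because it favours the safety claim and costs almost nothing to remove.

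**What to change.** Before analysis, delete the word palliative from item (3), so that any treatment of metastases found at staging counts whatever its intent. State also that resected metastatic tissue counts as residual tumour under item (1), so that the harm sentence is not applied to that operation. For a patient who meets item (3) and has a negative bowel re-resection, say that the patient counts as a missed case and that the re-resection is reported separately under harm.

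No extension to second tumours and no further Table 7 column are needed. The Data collection section already provides for details of additional tests and treatment in every patient with a neoplasm. General principles places the analysis after the plan is accepted for publication, so the wording can be settled beforehand. The cost is a few words and possibly a slightly higher missed count. The change concerns outcome scoring only and has no bearing on which treatment a patient receives.
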